**Table 3. Determination of disease progression, subsequent anti-tumor therapies, and data collection**

| Systematic review | Intracranial lesions | Extracranial lesions | Subsequent treatment                                                   | Subsequent anti-tumor evaluation                                                                               |
|-------------------|----------------------|----------------------|------------------------------------------------------------------------|----------------------------------------------------------------------------------------------------------------|
| PD                | PD                   | PD                   | Treatment discontinuation                                              | Continue evaluation until progressive disease as per RECIST 1.1 (all intracranial, extracranial, and systemic) |
| PD                | PD                   | Non-PD               | Treatment discontinuation                                              |                                                                                                                |
|                   |                      |                      | Continue aumolertinib + brain local treatment                          |                                                                                                                |
| PD                | Non-PD               | PD                   | Treatment discontinuation                                              |                                                                                                                |
|                   |                      |                      | Continue aumolertinib + extracranial local treatment (oligometastasis) |                                                                                                                |
| Non-PD            | PD                   | PD                   | Treatment discontinuation                                              |                                                                                                                |
| Non-PD            | PD                   | Non-PD               | Treatment discontinuation                                              |                                                                                                                |
|                   |                      |                      | Continue aumolertinib + brain local treatment                          |                                                                                                                |
| Non-PD            | Non-PD               | PD                   | Treatment discontinuation                                              |                                                                                                                |
|                   |                      |                      | Continue aumolertinib + extracranial local treatment (oligometastasis) |                                                                                                                |

### 9.1.3.5 Survival follow-up

For patients who have discontinued the study treatment, the patient or their family must be contacted once every 12 weeks from the time of treatment discontinuation to obtain survival information until their withdrawal from the study (withdrawal of informed consent, study termination or site closure, loss to follow-up, or death). In addition, details of subsequent anti-tumor treatment regimens and unresolved AEs must be collected, regardless of the date of last contact. The procedures include the following:

- Follow-up once every 12 weeks to document the details of subsequent anti-tumor treatments
- Follow-up once every 12 weeks to record subsequent response/progression data
- Follow-up once every 12 weeks to document the survival status

## 9.2 Unscheduled Visits/Tests

The investigator may perform unscheduled visits or examinations depending on the subject's condition, especially if the subject experiences an AE. An unscheduled visit and corresponding unscheduled examinations will be recorded in the eCRF, along with the reason for the unscheduled visit (or examination).

## 10.0 STUDY EVALUATION

### 10.1 Study-Specific Procedures

The requirements and instructions for each procedure and test/assessment indicator in the study schedule are detailed below.

#### **10.1.1 Informed consent process**

Informed consent must be obtained before subject enrollment and initiation of study procedures. Informed consent for participation in the study and informed consent for the sample collection should be included in the informed consent form at the time of enrollment.

#### **10.1.2 Screening number assignment**

Each patient will be assigned a unique screening number when informed consent is provided. The screening numbers of subjects who fail screening or withdraw from this study should not be reused.

#### **10.1.3 Screening and enrollment**

Each recruited subject must obtain the informed consent form before any study procedures are carried out, and then the subject will start screening.

Tumor assessments and other clinical data obtained prior to informed consent may not be repeated if they are completed within the time frame specified in the protocol. It is recommended that the screening process should start with the confirmation of EGFR mutation status.

The collection time of tumor tissues for EGFR mutation testing during the screening period may not be subject to the 28-day window, but the reported results should be no earlier than 3 months before the start of screening.

#### **10.1.4 Randomization number assignment**

Non-randomized design, with no need to assign a randomization number.

#### **10.1.5 Data collection**

The following data will be collected in the screening period according to the study plan (Appendix B):

Demographic data and other characteristics, including date of birth or age, sex, ethnicity, and smoking status.

Complete medical history: including past and current history of kidney, liver, blood system, gastrointestinal tract, endocrine, immune, metabolic, cardiovascular, respiratory, neurological, psychiatric, infectious, and inflammatory diseases. Treatment history: drug therapies (chemotherapy, prescription drugs, over-the-counter drugs, and other drugs) and non-drug therapies (e.g., surgery, radiotherapy).

Allergy history: Subjects' history of allergy to drugs or other substances.

#### **10.1.6 Physical examination**

Physical examinations will be performed once during the screening period, on C1D1, every 8 weeks in C2 and thereafter, and at the EOT visit according to the study plan (Appendix B).

Physical examination at baseline (defined as assessment performed before the start of study treatment) will cover the following systems: (1) eyes; (2) ears, nose, and throat; (3) heart and vascular system; (4) chest and respiratory system; (5) abdomen; (6) mucocutaneous system; (7) spine and extremities; (8) musculoskeletal system; (9) neurological system; (10) lymph nodes; (11) others. For subsequent routine physical examinations in each treatment cycle, significant changes from baseline should be evaluated for clinical relevance except for the neurological examination.

#### **10.1.7 ECOG PS score**

ECOG PS scoring will be performed once during the screening period, on C1D1, every 8 weeks in C2 and thereafter, and at the EOT visit according to the study plan (Appendix B).

0 = Fully active, able to carry on all predisease performance without restriction.

1 = Restricted in physically strenuous activity, but ambulatory and able to carry out work of a light or sedentary nature (e.g. light house work, office work).

2 = Ambulatory and capable of all self-care but unable to carry out any work activities. Up and about more than 50% of waking hours.

3 = Capable of only limited self-care, confined to bed or chair more than 50% of waking hours.

4 = Completely disabled. Cannot carry on any self-care. Totally confined to bed or chair.

5 = Dead.

#### **10.1.8 Body weight and height measurement**

Subjects will undergo body height and weight measurement according to the study plan (Appendix B).

#### **10.1.9 Vital signs measurement**

Vital signs measurement will be performed once during the screening period, on C1D1, every 8 weeks in C2 and thereafter, and at the EOT visit according to the study plan (Appendix B).

Vital sign measurements, including body temperature (oral or ear or axillary temperature, in °C, forehead temperature will not be acceptable), blood pressure (systolic and diastolic blood pressures), pulse, and respiratory rate, will be collected. Blood pressure and pulse are recommended to be measured after subjects sit for at least 10 min. Additional tests may be performed as deemed necessary by the investigator based on actual conditions.

#### 10.1.10 Laboratory tests

Laboratory tests will be performed once during the screening period, on C1D1, every 8 weeks in C2 and thereafter, and at the EOT visit according to the study plan (Appendix B).

Additional tests may be performed as deemed necessary by the investigator based on actual conditions. The values, units, and reference ranges for test results should be documented on the eCRFs.

The laboratory test items are shown in Table 4.

**Table 4. Laboratory test items**

| Clinical biochemistry              | Hematology                             | Urinalysis (qualitative)   |
|------------------------------------|----------------------------------------|----------------------------|
| Serum (S)/Plasma (P) — albumin     | Blood (B) — hemoglobin                 | U — urine specific gravity |
| S/P-ALT                            | B — leukocytes                         | U — pH                     |
| S/P-AST                            | B — hematocrit                         |                            |
| S/P — alkaline phosphatase         | B — red blood cell count (RBC)         |                            |
| S/P — bilirubin, total bilirubin   |                                        | U — urine protein          |
| S/P — Ca, total blood calcium      | B — neutrophil count and/or proportion | U — occult blood           |
| S/P — creatinine                   | B — lymphocyte count and/or percentage | U — nitrite                |
| S/P — creatine phosphokinase       | B — monocyte count and/or proportion   |                            |
|                                    | B — basophil count or percentage       |                            |
| S/P-LDH                            | B — eosinophil count or percentage     |                            |
|                                    | B — platelet count                     |                            |
| S/P — magnesium                    |                                        |                            |
| S/P — potassium                    |                                        |                            |
| S/P — sodium                       |                                        |                            |
| S/P — either urea nitrogen or urea |                                        |                            |

If the patient shows AST or ALT  $\geq 3 \times$  ULN and total bilirubin  $\geq 2 \times$  ULN, refer to Appendix C (Hy's Law) for actions required in case of a combined increase in aminotransferases and total bilirubin for further guidance.

#### 10.1.11 ECG

12-lead ECG will be performed once during the screening period, on C1D1, every 8 weeks in C2 and thereafter, and at the EOT visit according to the study plan (Appendix B).

Subjects are recommended to rest in a semi-supine position for at least 10 min before the given time point for 12-lead ECG. Subjects will undergo 3 separate ECG measurements at an interval of  $\leq 10$  min during each ECG measurement.

In this study, abnormal QT interval changes will be judged based on the mean of 3 QTcF intervals.

#### 10.1.12 Echocardiography

Echocardiography will be performed as clinically indicated throughout the treatment period according to the study plan to assess the left ventricular ejection fraction (LVEF).

When possible, one subject should undergo echocardiography performed by the same operator using the same machine throughout the study.

#### 10.1.13 Ophthalmological examination

During the screening period and throughout the study, ophthalmological examinations will be performed according to the study plan (Appendix B) and when clinically indicated, and it will be determined by the investigator as to which ophthalmological examination items are to be performed. Ophthalmological examination results should be documented on the eCRFs. Subjects who develop corneal ulcer will no longer be permitted to restart receiving the investigational medicinal product.

### 10.2 Efficacy Evaluation

#### 10.2.1 Response evaluation in solid tumors as per RECIST 1.1

During the oncological assessments by investigator, RECIST 1.1 will be used to assess the response to the anti-tumor treatment in each subject and calculate PFS, ORR, DoR, DCR, and DepOR. Appendix D provides the criteria in RECIST 1.1 for measurable lesions, non-measurable lesions, TLs, NTLs, complete response (CR), partial

response (PR), stable disease (SD), and progressive disease (PD). The analysis of the primary endpoint of this study will be based on the tumor response assessment made by the investigator as per RECIST 1.1, and the investigator will also manage the subjects based solely on the assessment results, unless medically contraindicated or faced with force majeure factors (such as update of the examination instrument by the study site). Baseline CT or MRI assessments of the chest, abdomen, and brain tissues must be performed within 28 days before the start of study treatment (not subject to the time of signing the ICF), and should be performed as close as possible to the start of study treatment. The investigator should perform additional imaging examinations based on subjects' signs and/or symptoms. The subsequent follow-up assessments should be performed using the method (CT/MRI) that is the same as that for baseline assessment. All enrolled subjects must have brain metastases as target lesions, and baseline imaging assessment of the brain must be performed, with MRI (enhanced) as the preferred examination method. Bone scans should be performed if there are indications for bone metastases (results within 3 months are acceptable), and positive sites found by bone scans should be confirmed by CT/MRI/X-ray. Only confirmed lesions can be recorded as non-target lesions. Subsequently, the bone metastases should be followed up by the same examination method as at baseline. During the study, bone scans may be added as needed. During the treatment period, tumor response assessment will be performed once every 8 weeks ( $\pm 1$  week) until progressive disease assessed by investigator per RECIST 1.1 (see Section 12.1.3 or 9.1.3.4). Tumor assessments should be performed according to the study plan whenever possible. If subjects are assessed at a time point beyond the scheduled time window ( $\pm 1$  week) and no progressive disease occurs, they should undergo subsequent assessments at the pre-specified time points whenever possible while continuing study treatment. If tumors are suspected at any other sites, the corresponding imaging examinations should be performed at the relevant sites. To achieve progression on the basis of the non-target lesion(s), there must be an overall level of substantial worsening in non-target lesion(s) such that, even in the presence of SD or PR in the target lesion(s), the overall tumor burden has increased sufficiently to merit discontinuation of treatment. A modest increase in the size of one or more non-target lesions is generally not sufficient to qualify for progression; therefore, it is uncommon to define overall tumor progression only with changes in non-target lesions in the face of SD or PR of target lesions. At each visit, objective tumor response will be assessed as per RECIST 1.1, and classified into CR, PR, SD, and PD. For the assessment of target lesion progression, the smallest lesion size in the entire course of treatment should be taken as reference, and an increase meeting the criteria will qualify for PD. If no progressive disease occurs, tumor response (CR and PR) and stable disease (SD) should be evaluated taking baseline lesion(s) as reference.

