| 02      | July 28, 2021    | 

1. Sample size calculation was performed based on the latest parameters. The number of subjects required to be enrolled was 63.

2. The primary endpoint, progression-free survival (PFS), is clearly defined as the 12-month PFS rate.

3. The inclusion criterion for subject's baseline intracranial lesion size was updated to <math>\geq 5</math> mm (previously <math>\geq 10</math> mm) following a review of large-scale clinical research literatures.

 |

19  
20

|                                                                                                                                                                                                                                                                                                                                                                                                                                                                                                                                                                                                                                                                                                                                                                                                                                                                                                                                                                                                                                                                                                                                                                                                                                                                                                                                             |                          |           |

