## **7.0 SCREENING OF SUBJECTS**

### **7.1 Inclusion Criteria**

A subject must meet all the following inclusion criteria in order to be enrolled in this study:

1. Age  $\geq 18$  years old.
2. Histologically or cytologically confirmed NSCLC, which is confirmed by imaging as advanced NSCLC with brain metastases (including stage IV patients who are newly diagnosed or have relapsed after previous surgical treatment; according to the AJCC 8th edition lung cancer staging criteria).
3. Confirmed as EGFR-sensitive mutations in tumor tissue samples or blood samples by local laboratory (including exon 19 deletion or L858R, either existing alone or co-existing with other EGFR site mutations). If tumor tissues are available, the tumor tissue is recommended for testing; if tumor tissues are not available or the patient cannot undergo tissue biopsy, blood samples may be tested.
4. Have not received any systemic treatment after the diagnosis of NSCLC with metastases to brain parenchyma. For patients who have received local treatment, the lesion within the scope of the local treatment cannot be used as the target lesion unless the lesion has progressed.
5. Patients with at least 1 extracranial target lesion (measurable lesions that have not undergone local treatment such as irradiation or have shown definitive after local treatment, with a baseline longest diameter  $\geq 10$  mm (or  $\geq 15$  mm for lymph nodes)) and at least 1 intracranial lesion (with a baseline longest diameter  $\geq 5$  mm).
6. The brain condition is stable or that were controlled with anticonvulsants or dexamethasone at a maximum dose of 5 mg daily before the study treatment.
7. An Eastern Cooperative Oncology Group (ECOG) performance status score of 0 or 1, with no worsening over at least 2 weeks before study treatment, and a minimum expected survival of 3 months.
8. Female patients of childbearing potential are willing to take appropriate contraceptive measures and should not breastfeed from signing the informed consent to 6 months after the last dose of study treatment; male patients are willing to take barrier contraception (i.e., condoms) from signing the informed consent to 6 months after the last dose study treatment.
9. Female patients of childbearing potential must have a negative serum or urine HCG test within 7 days before enrollment in the study, and they must be non-lactating.
10. The subject voluntarily participates and signs the informed consent form in writing.

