### **12.4 Statistical Analysis Methods**

#### **12.4.1 Definitions of statistical analysis sets**

- **Full analysis set (FAS)**

The FAS is defined as all patients with at least one dose of the study drug.

- **CNS evaluable-for-response set (cEFR)**

The cEFR is defined as a subset of the FAS and includes patients who have at least one measurable brain lesion. Baseline and demographic characteristics will be analyzed in the FAS and cEFR, and the efficacy evaluation will be performed in both the FAS and the cEFR. The results will be mainly based on the FAS.

- **Safety set (SS)**

The SS is defined as all patients who have received at least one dose of the study treatment. Safety evaluation will be based on the SS.

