#### 2.1 Measurable lesions

At least 1 non-irradiated lesion with the longest diameter of  $\geq 10$  mm (except for lymph nodes, which must have the short axis of  $\geq 15$  mm) that can be accurately measured at baseline and can be accurately remeasured by CT or MRI.

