#### 2.2 Non-measurable lesions

a. All other lesions, including small lesions (pathological lymph nodes with the longest diameter of  $< 10$  mm or the short axis of  $\geq 10$  mm to  $< 15$  mm at baseline; nodules with the short axis of  $< 10$  mm are considered non-pathological and should not be recorded as non-target lesions [NTLs]).

b. Truly non-measurable lesions include the following: bone lesions, submeningeal disorders, ascites, pleural/pericardial effusion, inflammatory breast diseases, lymphangitis of the skin or lung, and abdominal masses/abdominal organomegaly identified by physical examination, which cannot be measured by CT or MRI.

c. Previously irradiated lesions as local post-radiation changes that may affect the size of the lesion. Therefore, previously irradiated lesions will not be considered measurable and should be selected as NTLs at baseline and followed up as part of NTL assessment.

d. Skin lesions in clinical examination.

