### Special cases

- For TLs that can be measured in 2 or 3 dimensions, the longest diameter will be always reported. For pathological lymph nodes that can be measured in 2 or 3 dimensions, the short axis will be always reported.
- If the thickness of slices used in CT/MRI is  $> 5$  mm, the minimum size of measurable lesions at baseline should be twice the slice thickness on baseline scan.
- If the lesion disappears completely, the longest diameter should be recorded as 0 mm.
- If the TL splits into 2 or more parts, the sum of diameters of these parts should be recorded.
- If 2 or more TLs are combined, the sum of diameters of the combined lesions should be recorded, and the diameter of other lesions should be recorded as 0 mm.
- If the TL is believed to be present and is faintly seen but too small to measure, a default value of 5 mm should be assigned. If accurate measurements can be obtained, they should be recorded, even if they are below 5 mm.
- If the TL is too large to be accurately measured, an estimated value of the lesion size should be given.
- When any intervention is made to the TL during the study, such as radiotherapy, embolization, and surgery, the size of the TL should still be given where possible.

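### Every subject must have a brain target lesion and brain lesions of 5 mm qualify for entry, but Appendix D allows only lesions of at least 10 mm as targets, so patients with only 5–9 mm brain lesions cannot be assessed by the stated rules

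*Protocol*

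**What the plan says.** - **Entry.** Inclusion criterion 5 (Synopsis and section 7.1) asks for "at least 1 intracranial lesion (with a baseline longest diameter" of at least 5 mm. It does not itself call this lesion a target or measurable. The version history records that this threshold was lowered from 10 mm.
- **Brain target required.** Section 10.2.1: "All enrolled subjects must have brain metastases as target lesions". Section 9.1.3.4 likewise asks for at least one target lesion in the skull among at most five overall, with no further lesions selected for the intracranial evaluation.
- **What may be a target.** Section 10.2.1 names Appendix D as the source for measurable, target and non-target lesions. Appendix D 2.1 defines measurable as "At least 1 non-irradiated lesion with the longest diameter of" at least 10 mm (15 mm short axis for nodes). Sections 2.2, 2.4, 2.5 and 4.2.1 make smaller lesions non-measurable, draw targets from measurable lesions only, and turn the rest into non-target lesions. Section 4.3.1 does not require non-target lesions to be measured.
- **Analysis sets.** Section 12.4.1 describes the cEFR as the part of the FAS that "includes patients who have at least one measurable brain lesion". Efficacy is evaluated in both sets, but the results rest mainly on the FAS.
- **Scoring.** Appendix D Table 2: PR is a fall of at least 30% from the baseline sum; PD is a rise of at least 20% and at least 5 mm over the smallest sum. For a target judged "too small to measure, a default value of 5 mm should be assigned", unless an accurate smaller measurement is available.
- **Treated lesions.** Inclusion 4 lets a locally treated lesion serve as a target if it has progressed. Appendix D 2.2c says "previously irradiated lesions will not be considered measurable and should be selected as NTLs at baseline", with no exception for progression.

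**The concern.** A patient whose brain lesions all measure 5–9 mm is eligible, must have a brain target, and may not have one. This is exactly the group that the 5 mm threshold admits. No passage says which rule prevails. About 20 sites are planned, and the endpoints rest on investigator assessment, so the choice would be made site by site at baseline.

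An analysis plan may not be able to repair this afterwards. If a site records the lesion as non-target, its diameters need not be collected, and the other reading could be reconstructed only by re-reading scans. At stake are the intracranial response results, which are secondary endpoints but bear on the protocol's stated reason for the higher dose (sections 4.3.2 and 6.3).

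**Working it through.** The protocol gives no figure to reproduce. The check sets the rules side by side and applies Appendix D's own arithmetic.

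**1. A patient whose largest brain lesion is 5–9 mm**

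| | Site follows Appendix D | Site follows 9.1.3.4 and 10.2.1 |
|---|---|---|
| Lesion status | Non-target | Target |
| Possible intracranial result | CR, SD (Non-CR/Non-PD), PD, NE (Table 4, no target at baseline) | CR, PR, SD, PD, NE |
| Intracranial PR | Impossible | Possible |
| cEFR | Outside | Inside, if a target must be measurable; every subject then has one and cEFR = FAS |
| FAS | Inside | Inside |

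**2. Scoring of a lone intracranial target of baseline size b (mm)**

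PD size = max(1.2b, b + 5), where baseline is also the smallest sum. PR size = 0.7b or less. Change under the default entry = 5/b − 1.

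| b | PD at | Rise needed | PR at or below | Change if entered as 5 mm |
|---|---|---|---|---|
| 5 | 10 | +100% | 3.5 | 0%, not PR |
| 7 | 12 | +71% | 4.9 | −29%, not PR |
| 9 | 14 | +56% | 6.3 | −44%, PR |
| 10 | 15 | +50% | 7.0 | −50%, PR |

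The default entry blocks PR when 5 > 0.7b, that is when b is below about 7.1 mm (5/0.7). The 20% part of the PD rule governs only from a reference sum of 25 mm upwards (0.2 × 25 = 5).

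**3. Effect on the endpoints**

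- iORR and iDoR: under Appendix D these patients can respond only by CR, so FAS iORR falls and the set of responders who contribute to iDoR changes.
- iDCR: section 12.1.5 counts CR, PR and SD, so SD in place of PR leaves it unchanged.
- iPFS: one reading needs a 5 mm rise; the other needs unequivocal progression with substantial worsening of non-target disease. New lesions are PD under both. The direction of the difference cannot be derived.
- Systemic ORR and PFS: touched only because brain targets enter the overall sum.

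**4. Size, by assumption only**

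Let x be the share of patients with only 5–9 mm brain lesions and c their CR rate when handled as non-target. Neither is in the protocol. Take the CNS ORR of 60.9% quoted in section 4.2.4 as the rate in everyone else:

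FAS iORR = 0.609(1 − x) + xc

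- x = 20%, c = 0 to 20%: 0.487 to 0.527
- x = 40%, c = 0 to 20%: 0.365 to 0.445

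The cEFR under Appendix D would be 63 × 0.8 ≈ 50 or 63 × 0.6 ≈ 38.

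**The case against.** The strongest reply is that section 12.4.1 says measurable, section 10.2.1 sends the reader to Appendix D for that term, and Appendix D gives 10 mm. On that chain the cEFR is well defined, its description as a subset fits, and a cEFR result would stand beside the diluted FAS result. The intracranial endpoints are also secondary, with estimates and confidence intervals but no hypothesis or role in the sample size.

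Most of this stands, and it limits the point. A reader might infer that the cEFR cannot be derived at all; it can, from Appendix D alone. What fails is agreement with the rule that every subject has a brain target. A reader might also infer:

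- that a 5 mm lesion needs +100% growth where +20% would normally do. That comparator is wrong: a lone 10 mm lesion already needs +50%, and the non-target route does not use a percentage;
- that a small target can never show PR. Accurate measurements below 5 mm are to be recorded, and a lesion that disappears is entered as 0 mm;
- that the illustrated fall in iORR is an estimate. The 60.9% comes from independent review of 110 mg in second line, with a 95% CI of 38.5% to 80.3%, and the shares are assumed.

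The reply does not remove the contradiction. Reading Appendix D as controlling means disregarding two explicit sentences in the main text, and sites are not told to do so.

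**Conclusion.** Wrong as written. For patients whose only brain lesions measure 5–9 mm, inclusion criterion 5, the brain-target rule in 9.1.3.4 and 10.2.1, and Appendix D cannot all be followed. The consequence falls on the secondary endpoints iORR and iDoR, and on iPFS in an unproven direction. iDCR is little affected. The primary 12-month PFS rate and systemic ORR are touched only through the shared target sum, so the documents do not support reading this as a defect that undermines the primary analysis.

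The scoring figures in the table follow from Appendix D without assumptions, for a lone target whose baseline is its smallest sum. The overall size of the effect is unknown, because the protocol does not give the share of patients with only small brain lesions.

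The clash over irradiated lesions is separate and narrower. Inclusion 5 attaches its wording on treated lesions to extracranial disease, and prior whole-brain radiotherapy is excluded, so its reach in the brain is limited. It still needs one rule.

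**What to change.** Use one brain-lesion measurability threshold in 9.1.3.4, 10.2.1, 12.4.1 and Appendix D, settled before baseline lesions are selected. Eligibility need not change. Either:

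- **(a) Keep 10 mm.** Record 5–9 mm brain lesions as non-target, delete the requirement that every subject has a brain target in 10.2.1 and 9.1.3.4, define the cEFR as at least one brain lesion of at least 10 mm, and report iORR and iDoR in the cEFR beside the FAS; or
- **(b) Adopt 5 mm for brain.** Add a brain-specific rule to Appendix D with a matching MRI slice thickness and its own handling of lesions too small to measure, and define the cEFR to match. Appendix D's principle for thick slices, a minimum lesion size of twice the slice thickness, would imply slices of at most 5/2 = 2.5 mm if carried over.

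In either case, reconcile inclusion 4 with Appendix D 2.2c on irradiated lesions that have progressed.

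The cost is protocol wording and site instruction. Option (a) also shrinks the cEFR by the unknown share of patients with only small lesions: from 63 to about 50 or 38 if that share is 20% or 40%. Option (b) avoids that loss but makes demands on imaging at every site.
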